#### Onco-Move

Onco-Move is a relatively low intensity, home-based, individualized, self-managed physical activity program developed and tested in a pilot study by the Comprehensive Cancer Centre Amsterdam (IKA). Based on the "Every Step Counts" program of Mock [25,26], it uses self-management principles, aiming to maintain general physical fitness and preventing fatigue.

Trained nurses encourage patients to pursue an active lifestyle, 30 minutes per day, throughout the chemotherapy treatment, starting at the first chemotherapy session. Activities depend on patient preference, which may include walking, cycling, fitness training or swimming. Training with weights is not encouraged. At the first chemotherapy session, patients receive both verbal and written information about physical activity training, and specific advice about the desired intensity of activity based on the Borg Scale of perceived exertion (recommended level 12-14) [27]. The written information is based on the transtheoretical model of behavior [28,29], called "active living" which identifies different stages of activity (pre-contemplation, contemplation, action, and maintenance).

The information patients receive about physical activity is tailored to their activity stage. For example, patients in the contemplation stage receive more information on why and how to become active, while patients in the maintenance stage receive information on how to stay active [28,29]. Two weeks after the start of the program the nurse contacts the patient by telephone to inquire about how the program is going and if there is any additional information or advice needed. At each subsequent chemotherapy cycle, the nurse discusses program progress with the patient. Patients are asked to keep daily activity diaries, both to help them to monitor their own progress, and as an aid for the nurse to facilitate optimal use of the program.

#### OnTrack

The OnTrack is a relatively high intensity exercise program which is supervised by a physical therapist in an outpatient or general physical therapy practice setting. The pilot study showed that OnTrack was feasible in patients undergoing chemotherapy [30]. We are making use of the Onconet network of physical therapists in the region of North Holland who received special training in the OnTrack program. This facilitates patients to undergo the OnTrack program as close to home as possible.

In this program, patients are encouraged to be physically active for at least 30 minutes per day at Borg level 12-14 [27]. Like the Onco-Move program, patients are asked to keep a daily activity dairy. The physical therapists use the "active living" method to encourage daily physical activity. The physical therapist reviews the daily activity diary with the patient every three weeks.

Additionally, patients attend supervised exercise sessions two times per week. These sessions comprise exercises for warming up followed by exercises to maintain or increase muscle strength and exercises to maintain or increase aerobic capacity. Muscle strength exercises are performed for 20 minutes per session, starting with two series of 12 repetitions at 70% of the one repetition maximum (1RM) per exercise and increasing gradually to two series of eight repetitions at 80%1RM. Exercising in sets of two series is considered a sufficient, yet time efficient means of enhancing muscle strength, ensuring that all exercises can be performed during a session [31]. The resistance program consists of at least six exercises targeting the large muscle groups as follows: 1) vertical row (longissimus, biceps brachii, rhomboideus); 2) leg press (quadriceps, glutei, gastrocnemius); 3) bench press (pectoralis major, triceps); 4) pull over (pectoralis, triceps brachii, deltoideus, trapezius); 5) abdominal crunch (rectus abdominis); and 6) lunge (quadriceps, glutei, hamstrings). Additional exercises can be added according to patients' preferences.

For patients with breast cancer who have had axillary lymph node dissection, a modified strength training program is used for the upper extremities, consisting of two series of 15 repetitions for each exercise with the lightest possible weight, which is increased with the smallest possible step when the two series can be completed without symptoms of lymph edema [32].

Aerobic exercises are performed for 30 minutes per session (with a minimal duration of ten minutes per exercise), with an intensity of 50% to 80% of the maximal workload (Wmax) as estimated by the Steep Ramp Test [33]. The intensity of the aerobic exercises are increased if a patient scores a 12 or lower on the Borg scale of perceived exertion, while the intensity is decreased at a score of 16 or higher [27]. The heart rate should be within a heart rate zone of 60% to 90% of the maximal heart rate, which is conventionally estimated as 220 minus age.

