### Recruitment and randomization

In total 360 patients are being recruited from twelve community or university hospitals in the wider Amsterdam region of the Netherlands. All potentially eligible patients are identified by their medical oncologist or nurse practitioner, and receive written information about the trial. The patients are contacted by telephone to provide additional information about the trial and to confirm their eligibility. If the patient chooses to participate in the trial, (s)he is invited for an intake session where written informed consent is obtained and baseline assessments are made. Subsequently, patients are assigned to one of the three study groups by means of the minimization method [24], which is balanced on age, primary diagnosis, treating hospital and the use of trastuzumab.

Patients who decline to participate in the trial are asked to complete a one-time questionnaire assessing basic sociodemographic, attitudinal, and behavioral data, and to determine the reason(s) for non-participation.

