### Statistical analyses

All primary statistical analyses will be conducted on an intention-to-treat basis. Between group differences over time in performance indicators of general physical condition and muscle strength will be evaluated using multilevel regression analysis for % change from baseline, and two factor (group × time) multivariate analysis of variance with repeated measures on the time factor for comparison of mean scores. Scores on the self-report measures of fatigue, mood state and HRQoL will be calculated according to published scoring algorithms. Between-group differences over time in mean scores will be tested using a two factor (group × time) multivariate analysis of variance with repeated measures on the time factor. Effect sizes will be calculated using standard statistical procedures.

Supplementary analyses will be carried out in which data relating to compliance with the program elements are taken into account. Specifically, we will determine whether the level of compliance (based on attendance records and self-report data) is associated significantly with the changes over time in physical condition, muscle strength, fatigue, mood, and HRQoL. Similarly, we will investigate whether program effectiveness varies significantly as a function of patients' background characteristics, and particularly those variables assessing life style, health behavior and health attitudes.

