Several limitations of the trial should also be noted. First, although direct peakVO_2 _measurements are considered the gold standard for assessing cardiorespiratory fitness, these are not feasible in our trial because of the number and geographical spread of the training locations, and the (travel) time and costs involved with centralized measurements. However, it can be argued that an improvement in cycle endurance time may be more clinically relevant than an improvement in peakVO_2 _[50,51]. Second, although the usual care control group will not be provided with any materials or programs elements relating to physical exercise, clinicians and ancillary health care providers are increasingly recognizing the potential value of physical activity both during and following cancer treatment. Thus we cannot rule out the possibility that some patients in the control group will be encouraged to increase their level of physical activity, either by their caregivers or via the media. Nevertheless, we do not anticipate that this will take place in a structured or systematic way, and thus the planned comparisons (between the two intervention groups and the control group) will still be valid.

In summary, given the increasing number of patients with cancer, and improving survival rates, it is important to ensure that patients' physical and psychosocial health is maintained or even enhanced to as great an extent as possible both during active treatment and once treatment has been completed. Encouraging and facilitating physical activity during treatment may enhance health outcomes in both the short- and long-term.

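### The repeated-measures MANOVA named for fatigue and for performance mean scores ignores the nesting of OnTrack patients within training practices, so OnTrack standard errors may be somewhat too small

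*Protocol article*

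**What the plan says.** The OnTrack section of the protocol article describes a program "supervised by a physical therapist in an outpatient or general physical therapy practice setting". On who delivers it: "We are making use of the Onconet network of physical therapists in the region of North Holland who received special training in the OnTrack program". On location: "This facilitates patients to undergo the OnTrack program as close to home as possible". Contact is frequent: "patients attend supervised exercise sessions two times per week", from the first chemotherapy cycle until three weeks after the last (Interventions). The Discussion confirms that there are many sites, since direct peak oxygen uptake was ruled out partly "because of the number and geographical spread of the training locations".

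The other arms are organised differently. In Onco-Move, "Trained nurses encourage patients to pursue an active lifestyle, 30 minutes per day, throughout the chemotherapy treatment". Usual care varies by hospital, doctor and patient, and has no training practice. Patients are allocated individually by minimization, "balanced on age, primary diagnosis, treating hospital and the use of trastuzumab". The training practice is not a balancing factor.

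The Statistical analyses section names two methods for the performance outcomes: multilevel regression for percentage change from baseline, and, for mean scores, a "two factor (group × time) multivariate analysis of variance with repeated measures on the time factor". For fatigue, mood and quality of life it names only the MANOVA. Fatigue is a primary outcome. The levels of the multilevel regression are not named.

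**The concern.** Patients who train for months at the same practice may come to have similar outcomes if some practices deliver OnTrack more effectively than others. This source of variation exists in the OnTrack arm and has no counterpart in usual care, a design usually called partially nested. The repeated-measures part of the MANOVA deals with correlation between visits of the same patient. It has no term for correlation between patients of the same practice.

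If that correlation is positive, the test credits the OnTrack mean with more precision than it has. The OnTrack contrasts would then have standard errors that are too small and a type I error above the stated 0.05. Balancing or adjusting for treating hospital would remove this only so far as hospital and training practice coincide, and practices are chosen for closeness to home. The analysis would also not show whether the benefit varies between practices, which matters for a program meant to become part of standard care.

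**Working it through.** **Inputs from the protocol article.** Power calculation: 0.40 SD between OnTrack and usual care, 100 per group, power 0.80, two-sided alpha 0.05; 0.5 SD for fatigue; 360 patients recruited to three groups, so about 360/3 = 120 allocated to OnTrack.

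**Inputs assumed.** The article gives neither the number of OnTrack patients per practice (m) nor the ICC. I take m = 3, 6, 10 and ICC = 0.02, 0.05, 0.10. With 120 OnTrack patients these m imply 120/3 = 40, 120/6 = 20 and 120/10 = 12 practices.

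**Step 1: reproduce the stated sample size.** n per group = 2 × ((1.96 + 0.842)/0.40)² = 98.1, so 99 after rounding up. Power with 100 per group is 0.807. The stated 100 is thus a figure for independent patients, without an allowance for clustering.

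**Step 2: put clustering in the OnTrack arm only.** Take total SD 1 in both arms and equal arm sizes, and consider the pairwise contrast of OnTrack with usual care by normal approximation.

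- Design effect in the OnTrack arm: DE = 1 + (m − 1) × ICC; in usual care it is 1.
- Ratio of true to naive standard error: R = √((1 + DE)/2).
- True type I error of the naive test: 2 × P(Z > 1.96/R).
- Power at 100 per group once clustering is counted: Φ(d/√((1 + DE)/100) − 1.96), with d the difference in SD units.

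Worked example, m = 6 and ICC = 0.05: DE = 1 + 5 × 0.05 = 1.25; R = √(2.25/2) = 1.061; 1.96/1.061 = 1.848; type I error = 0.065.

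| m | ICC | DE | R | Type I error | Power, 0.40 SD |
|---|---|---|---|---|---|
| 3 | 0.02 | 1.04 | 1.010 | 0.052 | 0.800 |
| 3 | 0.05 | 1.10 | 1.025 | 0.056 | 0.788 |
| 3 | 0.10 | 1.20 | 1.049 | 0.062 | 0.769 |
| 6 | 0.02 | 1.10 | 1.025 | 0.056 | 0.788 |
| 6 | 0.05 | 1.25 | 1.061 | 0.065 | 0.760 |
| 6 | 0.10 | 1.50 | 1.118 | 0.080 | 0.716 |
| 10 | 0.02 | 1.18 | 1.044 | 0.060 | 0.773 |
| 10 | 0.05 | 1.45 | 1.107 | 0.077 | 0.724 |
| 10 | 0.10 | 1.90 | 1.204 | 0.104 | 0.651 |

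For the 0.5 SD fatigue difference, power at 100 per group is 0.942 without clustering and 0.836 in the worst row. For fatigue the issue is therefore the validity of the test more than a lack of power.

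**Step 3: which rows are plausible.** Many sites, spread out and chosen for closeness to home, point to few patients per practice. Ten per practice would mean only about 12 practices, which fits that description poorly.

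**The case against.** Five objections deserve an answer.

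- **The article is condensed, and multilevel regression is already named.** This stands for percentage change in the performance outcomes. A reader might infer that practice is missing from that model, or that every OnTrack contrast is affected. The document does not support this: the levels are simply not named, and practice may be one of them. The objection does not reach the MANOVA, which is a stated method with no place for practice.
- **A reader might infer that practice goes unrecorded.** The article does not show this. Its data lists are illustrative, and attendance records are kept.
- **Delivery is standardised.** Therapists received special training, the strength load follows a set scheme, aerobic intensity depends on the patient's own maximal workload and perceived exertion, and exercises are added at the patient's preference. This argues for a small ICC, and I accept it as such. It does not make the ICC zero.
- **Inflation is conditional.** Patients are randomised individually. If OnTrack had no effect in any practice, similarity between neighbours alone would not inflate the type I error. Inflation needs effects that differ between practices, and practices with more than one patient. This stands, and the conclusion is worded accordingly.
- **The other arms are not free of grouping.** All patients are nested in the twelve hospitals, and Onco-Move patients also in nurses. This is true, but hospital is common to all arms and used in the minimization. It does not offset variation found only in OnTrack.

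**Conclusion.** The point holds in a limited form. OnTrack is partially nested by practice, and the MANOVA named for fatigue and for performance mean scores treats patients as independent. Its OnTrack standard errors are too small if the effect of OnTrack varies between practices and practices train several patients each.

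The size rests wholly on assumed cluster sizes and ICCs. The likeliest range, with about 3 patients per practice, is a type I error of 0.052 to 0.062. With 6 it is 0.056 to 0.080. The figure of 0.104 is the extreme corner of the grid and should not be read as an estimate. This is a modest flaw in a stated method that is cheap to correct. It does not show that the trial's conclusions on OnTrack would be unreliable.

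**What to change.** For fatigue and for the performance mean scores, replace the MANOVA with a longitudinal mixed model that has a random practice effect in the OnTrack arm only. Patients in the other two arms enter as single units, and treating hospital enters as an adjustment factor. Name the same practice level in the multilevel regression for percentage change. Link each OnTrack patient to the training practice, for example from the attendance records, and report the between-practice variance beside the OnTrack effect.

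Nothing changes for patients or treatment. The cost is a change of method for the mean-score analyses (a MANOVA cannot simply take an extra term), one linking variable, and slightly wider confidence intervals for the OnTrack contrasts. If practices hold few patients each, the between-practice variance will be estimated imprecisely and should be reported with its uncertainty.

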#### Usual care

Usual care will vary according to hospital guidelines and doctors' and patients' preferences. Although usual care can not be standardized, it will not involve routine, systematic exercises.

### Study outcomes

All study outcomes, with the exception of return to work, compliance and satisfaction with the interventions, are assessed prior to randomization (T0), at the completion of chemotherapy (T1), and at 6 month follow-up (T2). Return to work is assessed at T1 and T2, while compliance and satisfaction are assessed at T1 only, and only in the two intervention groups.

To facilitate comparison of results across the A-CaRe studies, the outcome measures used in these four clinical trials have been harmonized to as great an extent as possible.

### Primary outcome measures

#### Cardiorespiratory fitness

Cardiorespiratory fitness is being assessed with the steep ramp test (an incremental bicycle ergometer test) and a cycle endurance test. Both tests are completed on a calibrated, electronically-braked cycle ergometer (Corival, Lode, Groningen, The Netherlands). For the steep ramp test, the patient is instructed to cycle at a speed between 70 and 80 revolutions per minute (RPM), starting with a 3 minutes warming-up at 10 Watts. The test starts at 25 Watts, after which the load is increased by 25 Watts every 10 seconds. The test ends if cycling speed falls below 60 RPM. Maximal workload (Wmax), time cycled at that load, and heart rate at the end of the test are recorded. The steep ramp test has been shown to be a reliable (ICC = 0.996) and valid (correlation with peak oxygen uptake (peakVO_2_) of 0.85) means of estimating maximal workload in patients with cancer. PeakVO_2 _can be estimated from the steep ramp test using a linear regression equation [33].

Exercise endurance is measured after a period of rest following the steep ramp test. The cycle endurance test is done at a workload based on 70% of the Wmax reached during the steep ramp test. After a one-minute warming-up on the same ergometer that was used for the steep ramp test, the load is increased to the predetermined workload. The patient continues cycling at this constant submaximal workload until the cycling speed falls below 60 RPM, with a maximum time of 30 minutes. The endurance time and heart rate at the end of the test are recorded. The workload of the endurance test used at follow up measurements is the same as that of the baseline endurance test.

#### Muscle strength

Upper extremity muscle strength is measured with the JAMAR^® ^grip strength dynamometer [34] and the microFET^® ^hand held dynamometer (HHD) for the elbow flexion, using a standardized measurement protocol [35]. Lower extremity muscle strength is tested with the microFET^® ^HHD for the extension of the knee, again using a standardized measurement protocol [36], and with the 30 s chair stands test. During the 30 s chair stands test patients are asked to stand up from a chair with their arms folded across the chest, then to sit down again. The action is repeated at their fastest pace over a 30 second period. The final test score is the number of times that the patient rises to a full stand from the seated position with arms folded within 30 s. The 30 s chair stands test has been shown to be a valid and reliable measure of proximal lower limb strength in older adults [37].

#### Fatigue

Fatigue symptoms are assessed with the Multidimensional Fatigue Inventory (MFI) [38]. The MFI is composed of 20 items, organized into five scales: general fatigue, physical fatigue, reduced activity, reduced motivation, and mental fatigue. Questions are posed about the past few days, and responses are recorded on a five-point scale.

In addition to the MFI patients are asked to complete the Fatigue Quality List (FQL) [39], assessing patients' perception and appraisal of experienced fatigue. The FQL consists of 25 adjectives describing the fatigue experience, organized into 4 subscales: frustrating, exhausting, pleasant, and frightening.

### Secondary study outcomes

Secondary outcomes are mood disturbance, quality of sleep, health-related quality of life, functioning in daily life, measured physical activity level, self-reported physical activity level, anthropometric measures, return to work, chemotherapy completion rates, compliance, satisfaction with the intervention, adverse effects and costs from a societal perspective. A complete overview of assessments and instruments are presented in Table 1. A small selection of these measures is described in detail.

**Table 1 T1:** Outcome measures

Assessment	Measurement instrument
**Primary Outcome measures**	

Cardiorespiratory fitness	Steep Ramp Test [33] Endurance Test

Upper Muscle Strength	JAMAR^® ^grip strength dynamometer [34] microFET^® ^HHD elbow flexion [35]

Lower Muscle Strength	microFET^® ^HHD extension knee [36] 30 s chair stands test [37]

Fatigue	MFI [38] FQL [39]

**Secondary Outcome measures**	

Mood disturbance	Hospital Anxiety and Depression Scale (HADS) [52]

Quality of sleep	Pittsburgh Sleep Quality Index (PSQI) [53]

Health-related quality of life	EORTC QLQ-C30 [32]

Functioning in daily life	Impact on Participation and Autonomy (IPA) [54]

Measured physical activity level	Actigraph accelerometer

Self-reported physical activity level	Physical Activity Scale for the Elderly (PASE) [55]

Anthropometric measures	Skinfold measurements (Harpenden) Waist and hip circumferences [56]

Return to work	Return to work questionnaire

Chemotherapy completion rates	Medical records

Compliance	Number of sessions attended and activity diary

Satisfaction with the intervention	Satisfaction questionnaire

Adverse effects	Medical records

Costs from a societal perspective	EuroQol EQ5D [42] and monthly cost diaries

#### Measured physical activity level

The level of physical activity will be objectively measured with the Actigraph (Actigraph, Fort Walton Beach Florida, USA), a small accelerometer which can measure accelerations from 0.05 to 2.00 G [40]. These accelerations are scored in counts per minute that provide information about how long and how intensive a patient has been physically active. The epoch will be set at 5 seconds. Patients wear the accelerometer on the right hip for 5 days including at least one weekend day. The Actigraph will not give any form of feedback to the participant.

